#### *9g. Data entry and storage*

Screening and CRF data will be entered by study staff onto Android-based tablet computers programmed for data collection using the REDCap mobile app. The REDCap system provides a secure, web-based platform for data entry that allows real time monitoring, querying, and quality control of data by an off-site data manager. It allows access to data to be assigned and restricted to individual study staff as needed and creates audit trails to monitor appropriate access. The mobile app allows data to be entered offline and then uploaded to a central server when an internet connection is available. Records are encrypted upon entry and can be removed from data capturers' tablets once they have been uploaded to the server, reducing the chances of breach of confidentiality if a tablet is lost or stolen. REDCap is supported by the Boston University IT office (<https://redcap.bumc.bu.edu/>). It has previously been used successfully in South Africa, where the University of the Witwatersrand is a REDCap Consortium partner.

Medical record data for study subjects will be downloaded from electronic medical record systems where available. The lead data analyst will be responsible for ensuring that study identification numbers are correctly matched to the record numbers in the database. In instances where the data analyst cannot match a study ID number to an electronic medical record number using only the fields in the study linking file, a query will be sent to the on-site study staff, who will access the clinic's paper-based patient files to determine whether the subject ever initiated ART and, if so, locate the correct medical record number.

At sites where all or some data are recorded only in individual paper-based files, a note or tab indicating that a patient is a participant in the study will be attached to the cover of each subject's file, to assist site and study staff in locating study subjects' files for data extraction. At regular intervals, files will be pulled and the data fields listed above entered into the study database by study staff. All data entry will take place at the study clinics or other locations where the files are stored; no hard copies of patient records will be taken off site by the study team.

Data will be retained in secure study databases until completion of the study, including completion of all data analysis and report writing associated with the study and closing of the IRB-approved protocol. Study data sets and other electronic files containing study data will then have all identifiers removed

and where possible will be made available for use of other researchers through a repository such as Dryad. Hard copies of study documents will be shredded.

## **10. Staff Supervision and Training**

In each study country, the local study team will include a principal investigator, study coordinator, and site-based study clinicians, assistants, and data capturers. The local PIs will be responsible for training and supervising their teams, under the guidance of the overall study PI and co-investigators. The study clinicians who will implement the intervention will have the qualifications required for ART initiation in each study country. Study assistants who will administer consent and the questionnaire will also be trained as HIV counselors to ensure that they are sensitive to the needs of HIV-positive study subjects.

All members of the study team will be trained in and adhere to the standards laid out in the Belmont Report and NIH guidelines for research and in research ethics applicable to South Africa. Human subjects ethics training will be repeated on an annual basis to ensure that the study team's understanding of research ethics is current.

## **11. Sample Size**

Using results of the RapIT randomized trial we recently conducted in South Africa, we estimate that 65% of treatment-eligible patients will be initiated on antiretroviral therapy and retained on ART in the standard group, and we consider an increase to 80% to be programmatically important. Using an  $\alpha$  of 0.05, power of 90%, 1:1 randomization, and an uncorrected Fisher's exact test, this requires a minimum sample size of 197 patients per group, which we will increase to a maximum of 240 per group to ensure sufficient power if patients withdraw or are found ineligible after consent, or 480 per country.

In addition, in South Africa only, we would like to be able to compare between study sites the proportions of patients in the intervention group who screen in and screen out of the SLATE algorithm. Based on early enrollment, we expect the proportion screening in to be a maximum of 67%, which we will conservatively reduce to 60%. We expect the proportion screening in to be a minimum of 32%, which we will conservatively increase to 35%. With an  $\alpha$  of 0.05 and power of 90%, we estimate that we will need to enroll a minimum of 79 patients in the intervention arm per site, or a minimum of 158 participants in both arms per site. In order to maintain constant enrollment periods at all three sites in South Africa, we will continue to enroll until the slowest site has reached a minimum of 158. We anticipate that total enrollment at that point will be a maximum of 660 participants in South Africa.

The sample size will thus be a maximum of 480 in Kenya and 660 in South Africa, or a maximum of 1140 for the two-country study.

## **12. Outcomes and Data Analysis**

### *12a. Outcomes*

The primary outcomes for the study are:

1. The proportion of patients initiated on ART within 28 days of study enrollment. While national guidelines recommend ART initiation within two weeks of a patient's first clinic visit or HIV diagnosis, recent studies suggest that 28 days is a more realistic deadline for routine care.

2. The proportion of patients who initiate ART and are alive, in care, and retained on ART eight months after study enrollment. Eight months was selected to allow up to 1 month (28 days) to initiate ART, six months of follow up after treatment initiation, and up to 1 month to return for the six-month routine clinic visit.

These outcomes were proposed in a paper published by the investigators based on the MATI technical consultation described in protocol section 3c.

Secondary outcomes will include:

3. The proportion of patients initiated on ART within 14 days of having an HIV test or enrolling in HIV care.
4. The proportion of patients who initiate ART and are virally suppressed eight months of having an HIV test or enrolling in HIV care between HIV-infected patients offered immediate ART initiation under the SLATE algorithm and patients offered standard ART initiation.
5. The proportions of patients who initiate ART and are alive, in care, and retained on ART 14 and 16 months after having an HIV test or enrolling in HIV care. Fourteen months extends the primary outcome endpoint, which is at 8 months, by an additional six months. Sixteen months allows loss to follow up at 12 months to be defined as three months late for the 12-month visit, which is a common endpoint in the literature (16 = 1 month to initiate ART + 12 months' follow up + 3 months to attend 12-month visit).
6. The proportions of HIV-positive patients presenting at study clinics and not yet on ART who are eligible and ineligible for immediate initiation using SLATE algorithm criteria.
7. Reasons for ineligibility for immediate initiation, among those found ineligible in the intervention arm.
8. Average time to ART initiation (days) for each arm.
9. Patient preferences on the speed and timing of ART initiation.
10. Costs to patients of ART initiation under standard and intervention procedures.
11. Costs to providers of ART initiation under standard and intervention procedures.

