##### *4b. Secondary objectives*

The secondary objectives of this study are to:

3. Compare the proportion of study-eligible patients who initiate ART within 14 days of study enrollment between HIV-infected patients offered immediate ART initiation under the SLATE algorithm and patients offered standard ART initiation.
4. At sites where viral load data are available, compare the proportion of study-eligible patients who initiate ART and are virally suppressed eight months after having an HIV test or enrolling in HIV care
5. Compare the proportion of study-eligible patients who initiate ART and are alive, in care, and retained on ART by 14 months and 16 months after study enrollment between HIV-infected patients

offered immediate ART initiation under the SLATE algorithm and patients offered standard ART initiation.

6. Estimate the proportion of HIV-positive patients presenting at study clinics and not yet on ART who are eligible or ineligible for immediate initiation using SLATE algorithm criteria.
7. Describe reasons for ineligibility for immediate initiation, among those found ineligible in the intervention arm.
8. Estimate average time interval in days between study enrollment and ART initiation for each study arm.
9. Describe self-reported patient preferences on the speed and timing of ART initiation.
10. Estimate costs to patients of implementing the SLATE algorithm, compared to standard care.
11. Estimate costs to providers of implementing the SLATE algorithm, compared to standard care.

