#### *Inclusion criteria:*

- Adult patients ( $\geq 18$  years) (initiating children on ART is likely to require additional information, making the SLATE algorithm less applicable to pediatric populations)
- Confirmed HIV-positive test result at any time (may have been diagnosed previously)
- Not currently on ART (three-drug combination)
- Presented at the study clinic for any HIV-related reason, including an HIV test, pre-ART monitoring, or ART initiation

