#### *9e. Medical record data*

Once the CRF has been completed, all remaining patient-level data for the study will be collected from routinely maintained medical records. The format of these records will vary by study country and site. Some sites will use electronic medical records, while others will rely on paper-based records and registers or a combination of electronic and paper. We will access all available records for each study

patient, regardless of format or storage location, to try to obtain as complete a study data set as possible. The fields we will aim to capture are listed below.

*To be used to link electronic and paper-based records to study identification number only:*

- Electronic medical record system number
- Clinic file numbers
- National ID number
- Name
- Date of birth
- Sex

*All subjects at clinic visit on date of study enrollment:*

- Date of positive HIV test (if available)
- CD4 count (most recent)
- Date and result of TB symptom screen, if done
- Date, type, and result of TB test(s) (current and previous, if any)
- TB treatment, if offered (date of initiation)
- WHO stage and clinical conditions

*Subjects who are eligible for ART initiation at the study clinic:*

- Reasons for delaying ART initiation, if relevant
- Date ART initiated (first dose of drugs dispensed)
- First-line regimen prescribed

*For all clinic visits for duration of study follow up, from study enrollment to the follow-up endpoints indicated above:*

- Date of visit
- Primary reason for visit (e.g. pre-ART visit, scheduled medical visit, medication pickup, unscheduled medical visit)
- Types of professionals seen (e.g. nurse, doctor, pharmacy assistant, counselor)
- Group and individual sessions attended (e.g. wellness course, adherence education)
- Numbers and types of all lab tests conducted (including CD4 counts, viral loads, CrAg test, blood tests to determine ARV regimen)
- Other procedures (e.g. x-rays) performed
- Medications prescribed and dispensed (ARV and non-ARV, including isoniazid and cotrimoxazole)
- Admissions for inpatient care since previous visit, if recorded
- Details of inpatient care received (facility, number of days, medications, lab tests, etc.) if recorded

*At follow-up endpoints (6 and 12 months after ART initiation or comparable timepoint for those who do not initiate ART):*

- Date and result of most recent viral load test

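### Section 12a starts the clock for secondary outcomes 3 and 5 at an HIV test or entry into care, contradicting the enrollment origin in section 4b; outcome 4 uses the test-or-care origin in both places, out of line with the primary outcomes

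*Protocol*

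**What the plan says.** The protocol gives these time origins for its five comparative clinical outcomes:

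| Outcome | Section 4 (objectives) | Section 12a (outcomes) |
|---|---|---|
| Primary 1, initiation by 28 days | study enrollment | study enrollment |
| Primary 2, retention at 8 months | study enrollment | study enrollment |
| Secondary 3, initiation by 14 days | "who initiate ART within 14 days of study enrollment" | "The proportion of patients initiated on ART within 14 days of having an HIV test or enrolling in HIV care" |
| Secondary 4, suppression at 8 months | "virally suppressed eight months after having an HIV test or enrolling in HIV care" | "virally suppressed eight months of having an HIV test or enrolling in HIV care" |
| Secondary 5, retention at 14 and 16 months | "retained on ART by 14 months and 16 months after study enrollment" | "retained on ART 14 and 16 months after having an HIV test or enrolling in HIV care" |

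The inclusion criteria in section 5c accept a "Confirmed HIV-positive test result at any time (may have been diagnosed previously") and patients who attend for pre-ART monitoring, provided they are not on ART at the time. Section 9e lists, for abstraction from records, "Date of positive HIV test (if available"). The questionnaire described in section 9d also asks about time of diagnosis.

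**The concern.** For outcomes 3 and 5 the protocol states two different clocks for the same endpoint. For outcome 4 it states one clock, but not the one used for the primary outcome at the same 8-month mark. If every patient were tested and entered care on the day of enrollment, the difference would be harmless. The eligibility criteria say otherwise, so the clock can start before randomisation.

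Three things are at stake:

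- On outcome 3, some patients are certain failures whatever arm they are in.
- On outcomes 4 and 5, the length of post-randomisation follow-up differs between patients and can be zero or negative.
- The origin is one date or another, with no rule for patients in whom the two differ. The endpoint is therefore not fully defined, and the results cannot be read beside the primary outcomes.

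**Working it through.** **Step 1. Which clock does the rest of the protocol assume?** Section 12a explains 14 months as the 8-month primary endpoint plus six months, which works only if both run from enrollment. It builds 16 months as 1 month to initiate + 12 months of follow-up + 3 months to attend, which does not fit a clock that started well before enrollment. Sections 5c and 8 both count record follow-up from enrollment (they differ on its length, a separate matter), and section 9e collects visits from enrollment onward. All of this points to enrollment.

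**Step 2. Outcome 3.** Let d be the days from the applicable origin to enrollment, and s ≥ 0 the days from enrollment to ART start. The patient is off ART at enrollment, and I take the initiation that counts to be the one after enrollment. Time from origin to ART is d + s.

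- If d > 14, then d + s > 14 even at s = 0. The patient fails in either arm, same-day start included.
- If 0 < d ≤ 14, the window left after enrollment is 14 − d days instead of 14.

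**Step 3. Outcomes 4 and 5.** With an origin m months before enrollment, the time left after randomisation is 8 − m, 14 − m and 16 − m months.

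| m | Outcome 4 (8 months) | Outcome 5 (14 months) | Outcome 5 (16 months) |
|---|---|---|---|
| 0 | 8 | 14 | 16 |
| 6 | 2 | 8 | 10 |
| 8 | 0 | 6 | 8 |
| 16 | −8 | −2 | 0 |

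**Step 4. Can the origin be dated?** The definition joins two dates with an *or* and does not say which governs. The record test date is taken only where it exists; the questionnaire's time of diagnosis partly fills that gap. Section 9e lists no field for the date of entry into HIV care.

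**Step 5. Size for outcome 3.** The protocol gives no 14-day proportions, so I borrow the 65% and 80% of section 11, which were set for initiation plus retention. The stated 197 per group for those inputs reproduces as 198 (two-sided 5%, 90% power, continuity-corrected normal approximation); it does not depend on outcome 3.

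Let f be the share of patients with d > 14. They score zero in both arms. If the effect is the same in everyone else:

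- standard arm: 0.65 × (1 − f); intervention arm: 0.80 × (1 − f)
- risk difference: 0.15 × (1 − f)
- risk ratio: 0.80 / 0.65 = 1.23 at every f

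Power below is two-sided at 5%, uncorrected. The 240 per group is the planned country maximum before the South African increase; 570 is the pooled maximum of 1140 halved.

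| f (assumed) | Standard | Intervention | Risk difference, points | Power, 240 per group | Power, 570 per group |
|---|---|---|---|---|---|
| 0 | 65.0% | 80.0% | 15.0 | 96% | above 99% |
| 20% | 52.0% | 64.0% | 12.0 | 76% | 98.5% |
| 30% | 45.5% | 56.0% | 10.5 | 63% | 94.5% |
| 50% | 32.5% | 40.0% | 7.5 | 40% | 75% |

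**The case against.** The best defence is that the intended clock is plain. Objectives 3 and 5, the rationale for 14 and 16 months and the follow-up rules all point to enrollment, so the 12a wording looks carried over from elsewhere and an analyst would probably use enrollment anyway. That is fair for outcomes 3 and 5, but it is a reason to correct 12a, not to leave it. It does not help outcome 4, where objective and outcome agree on the other origin.

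Four stronger readings are tempting, and the protocol does not support them:

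- *Every previously diagnosed patient fails outcome 3.* No. A patient tested long ago who first enters HIV care at the study visit may be dated correctly under the second half of the definition. Those affected are patients whose applicable date precedes enrollment, and patients in pre-ART monitoring are the clearest case. The share f is therefore not simply the share diagnosed earlier.
- *Sections 4b and 12a contradict each other on all three outcomes.* Only on 3 and 5. For outcome 4 the criticism is misalignment with the primary outcome.
- *All three effects are diluted toward zero.* This is shown only for the outcome 3 risk difference. Section 12b also reports risk ratios, and in the same model the risk ratio does not move. For outcomes 4 and 5, an intervention that speeds initiation could show a larger or a smaller difference when assessed sooner after randomisation.
- *The comparison is biased.* Randomisation spreads these patients evenly between arms on average.

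It is also true that only secondary outcomes are involved, and that pooled power stays high at moderate f in the illustration.

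**Conclusion.** The text is wrong as written and should be fixed. Outcomes 3 and 5 have contradictory time origins in 4b and 12a, and outcome 4 has an origin that does not match its 8-month primary counterpart. Applied literally, 12a makes patients with an applicable date more than 14 days before enrollment certain failures on outcome 3. It also gives outcomes 4 and 5 unequal follow-up that can end before randomisation.

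The harm is a diluted risk difference on outcome 3, lost precision and ill-defined endpoints, not bias between arms. The figures in the illustration rest on three assumptions: a value of f, which the protocol does not give; 14-day proportions borrowed from section 11; and an equal effect in all patients not forced to fail. The logical result for outcome 3 needs none of these, only that the initiation counted is the one after enrollment. Both primary outcomes and the sample size stand.

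**What to change.** In section 12a, make study enrollment the origin for outcome 3 (14 days), outcome 4 (8 months) and outcome 5 (14 and 16 months). Make the same change to objective 4 in section 4b. Objectives 3 and 5 already read correctly. Keep time since diagnosis, from the section 9d questionnaire, as a baseline descriptor so that newly and previously diagnosed patients can be told apart. Any separate analysis plan should carry the same origin.

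The cost is a wording amendment. No new data are needed: the enrollment date is known for everyone and record follow-up is already counted from it.

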### *3b. The problem: loss to follow up before treatment initiation*

Studies from throughout sub-Saharan Africa continue to document high losses of treatment-eligible patients from care before they receive their first dose of ARVs. A systematic review of the literature on pre-ART retention in care found that roughly one third of adult patients in sub-Saharan Africa who had already been determined eligible for ART did not start ART within the studies' follow-up periods. If those diagnosed with HIV but not assessed for treatment eligibility had been added, this proportion would have been far higher. Reasons for this include a wide range of facility- and patient-level barriers to initiation. Among facility-level barriers are clinic inaccessibility and inefficiency and initiation protocols designed for the convenience of providers rather than patients. These barriers manifest themselves as multiple required visits, long waiting times, stock outs of supplies, staff absences, and poor communication between staff and patients. Eliminating the eligibility threshold under a "treat all" policy is not likely to solve these problems, as clinics become even more crowded with newly-eligible patients. Simpler, more efficient, accelerated algorithms for ART initiation will be needed if "treat all" is to realize the benefits expected.

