##### *Primary outcomes 1 and 2 and secondary outcomes 3, 4, and 5:*

For all primary and secondary clinical outcomes, the analytic approach will be the same. All analyses will be by intention-to-treat: subjects will be analyzed according to the intervention they were supposed to receive, whether or not they adhere to the defined intervention. This includes patients randomized to the intervention arm who are screened out of immediate ART initiation by the SLATE algorithm; they will remain in the intervention arm for data analysis. Primary analyses will be pooled across study countries, though we will also conduct stratified analyses by country to look for country-specific differences.

The analysis will begin with a simple comparison of the two treatment groups with respect to baseline predictors of outcomes to look for any imbalances. These potential confounders include demographic

(e.g. age, sex) and socioeconomic (education, distance from clinic, employment, etc.) variables, medications, baseline CD4 counts, and low BMI, among others.

We will then conduct a crude analysis comparing the proportion of patients achieving each dichotomous outcome by group and estimating crude risk ratios and crude risk differences and their corresponding 95% confidence intervals. This will be our primary analysis as we anticipate that randomization of over 1000 subjects should lead to balance in baseline covariates. Should any important imbalances occur by chance, we will proceed with an adjusted model as described below for the country-specific analyses.

Next, we will look for effect modification by important predictors of each outcome. The primary modifier will be country, as practices for care and treatment may differ across the different countries. We will also look for differences in effects stratified by age, sex, baseline BMI, CD4 count, and any other important demographic and clinical predictors of outcomes identified. Our analysis for effect modification will use a simple stratification of the primary analysis by the potential modifier and report crude risk differences and risk ratios and their corresponding 95% confidence intervals.

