#### *Secondary outcomes 6-9:*

Secondary outcomes 6, 7, 8, and 9 are descriptive in nature. These will be described using frequencies, stratified by country, site, and patient characteristics as numbers allow.

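### Secondary outcome 8 averages days to ART initiation, which do not exist for patients who never start, so each arm's figure describes a different, non-randomized subset

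*Protocol*

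**What the plan says.** Section 12a lists outcome 8 as "Average time to ART initiation (days) for each arm". The matching objective in section 4b is worded "Estimate average time interval in days between study enrollment and ART initiation for each study arm". Section 12b groups it with outcomes 6, 7 and 9 as descriptive and adds: "These will be described using frequencies, stratified by country, site, and patient characteristics as numbers allow".

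None of these places says how a patient who never starts ART enters the average. There is no censoring rule, no time horizon and no label restricting the figure to starters. The intention-to-treat statement in section 12b stands under the heading "Primary outcomes 1 and 2 and secondary outcomes 3, 4, and 5", which does not include outcome 8.

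The protocol plainly expects non-starters. Section 9e plans an endpoint at a "comparable timepoint for those who do not initiate ART", and section 3b cites a review in which "roughly one third of adult patients in sub-Saharan Africa who had already been determined eligible for ART did not start ART" within follow-up.

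**The concern.** Starting ART happens after randomization, and it is the event the intervention is designed to make more common (section 4a, objective 1). A mean of observed days can be taken only over patients who started. That group is a different selection in each arm, so setting the two figures side by side is not a randomized comparison. The summary also omits what the trial is mainly about: a patient moved from never starting to starting adds nothing to it except a new value in the intervention average.

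Frequencies do not repair this. They do not produce an average, and they do not deal with patients who have no event.

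At stake is the reading of the only outcome that expresses speed in days. The figure also depends on how late a start is still counted, and the length of record review is given as up to 16 months in section 5c but up to 14 months in section 8.

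**Working it through.** **The plan's own figures.** No number is stated for outcome 8. The planning rates in section 11 are 65% and 80%. The stated minimum of 197 per group for these rates reproduces: the continuity-corrected normal approximation gives 198, and exact two-sided Fisher power at 197 is 90.1%.

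**How many patients could lack a value.** Section 11 says "we estimate that 65% of treatment-eligible patients will be initiated on antiretroviral therapy and retained on ART in the standard group". This rate requires retention as well as initiation, so the share who start is at least as large. With 1140/2 = 570 per arm, patients without a value number at most 0.35 × 570 ≈ 200 in the standard arm and 0.20 × 570 = 114 in the intervention arm.

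**Size of the discrepancy.** Inputs:
- Share screening in, s: 32% to 67%, the extremes expected in section 11 for South African sites.
- Standard-arm share starting, p: 65%. This is an assumption, because the section 11 figure also includes retention.
- Standard-care start time, m: day 25 for every starter. This is an assumption; the protocol gives no figure.
- Patients who screen in start on day 0. Those screened out behave like the standard arm, to which section 7c refers them. Both are assumptions.
- Eight months is taken as 240 days.

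Formulas for the SLATE arm:
- Share starting = s + (1 − s)p
- Mean among starters = (1 − s)pm / [s + (1 − s)p]
- Mean time without ART to horizon H = (1 − s)pm + (1 − s)(1 − p)H

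Setting s = 0 gives the standard arm. For example, at H = 240 the standard arm has 0.65 × 25 + 0.35 × 240 = 100.25 days, and SLATE at s = 0.32 has 0.442 × 25 + 0.238 × 240 = 68.17 days.

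| Summary (days) | Standard | SLATE, s = 32% | SLATE, s = 67% | Gain |
|---|---|---|---|---|
| Share starting | 65.0% | 76.2% | 88.5% | – |
| Mean among starters | 25.00 | 14.50 | 6.06 | 10.5 to 18.9 |
| Without ART to day 28, all patients | 26.05 | 17.71 | 8.60 | 8.3 to 17.5 |
| Without ART to day 240, all patients | 100.25 | 68.17 | 33.08 | 32.1 to 67.2 |

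**Sensitivity to 65%.** Section 3b reports a risk ratio of 1.36 for starting in the earlier same-day trial. Since no rate can exceed 100%, its standard arm started at most 1/1.36 = 73.5%. With p = 0.735 the gains are 9.8 to 18.4 days among starters and 26 to 55 days to day 240. The pattern is the same.

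**Direction.** Under the model above the starters' mean cannot rise, because (1 − s)p / [s + (1 − s)p] is below 1 for any s above 0. A reversal needs a different pattern. Suppose the same 65% start at mean m1 under SLATE instead of m0, and a further 15% start who otherwise would not. The starters' mean rises only if those extra patients begin on average later than (0.80 × m0 − 0.65 × m1)/0.15:
- m0 = 14, m1 = 10: day 31
- m0 = 14, m1 = 0: day 75
- m0 = 30, m1 = 0: day 160

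As an illustration with assumed days, take m0 = 14, m1 = 10 and the extra 15% at day 60. The mean among starters is 14.0 days for standard care and (0.65 × 10 + 0.15 × 60)/0.80 = 19.4 days for SLATE, although no patient is worse off. Time without ART over all patients is 18.9 versus 16.3 days to day 28, and 93.1 versus 63.5 days to day 240.

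**The case against.** The strongest reply is that little hangs on this. Objectives 1 to 5 compare the arms, while objective 8 only estimates a figure for each; no test, interval or difference is planned for it. Speed in all randomized patients is already captured at two points, 14 and 28 days, with risk ratios and risk differences. The word average does not strictly mean a mean among starters: an all-randomized median exists whenever more than half of an arm starts. The denominator of a descriptive outcome could also be settled in a statistical analysis plan.

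Most of this stands and limits the weight of the point. It does not remove it. The protocol goes beyond silence on detail: it names a summary that is undefined for patients it expects to have, and a method that does not yield that summary. An analysis plan that follows the text literally inherits the problem.

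Two stronger readings are tempting but unsupported:
- A reader might infer that the averages will make SLATE look slower. Reversal needs the additional starters to begin late. Section 3b reports that in the earlier same-day trial 75% of the intervention arm started on the day of enrollment and nearly all the rest within a month.
- A reader might infer that the benefit is understated about threefold. That ratio comes from counting non-starters to day 240; at 28 days the all-patient gain is slightly smaller than the starters-only gain. Delay among starters and time without ART are also different quantities, so their ratio does not measure bias.

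**Conclusion.** The point holds as a moderate defect in a secondary, descriptive outcome. As worded, outcome 8 has no value for patients who never start, so a mean of observed days compares non-randomized subsets and leaves out the gain from additional starters. Primary outcome 1 and secondary outcome 3 are unaffected, and the sample size does not depend on it.

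The numerical gap is small at 28 days and larger at eight months. These figures rest on assumed start times, on same-day starts for everyone who screens in, on unchanged behaviour in those screened out, and on reading 65% as a start rate. The direction of the averages is not shown to be wrong; reversal remains a theoretical possibility.

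**What to change.** - In sections 4b and 12a, define outcome 8 as time from enrollment to ART initiation in all randomized patients.
- In section 12b, take outcome 8 out of the group described by frequencies. Report cumulative incidence of initiation by arm, with death before initiation as a competing event.
- Add one all-randomized summary with a 95% interval: the median, where more than half of an arm starts, or the restricted mean time without ART to a stated horizon such as 28 days or 8 months. If the restricted mean is used, state how time after death is counted.
- Keep an average among starters only if it is labelled as such and shown beside the proportion who started.
- Reconcile the 14-month and 16-month follow-up statements, so that the period over which a start counts is fixed.

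The cost is wording in these sections and a little more analysis. Section 9e already provides for abstracting dates of initiation and of death, so no new data are needed.
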